### Ethics

This study has been reviewed and approved by the Queen Mary Ethics of Research Committee on the 9^th^ of February 2022 and the approval is valid for 3 years from the date of approval–Reference Number: QMERC20.601. In accordance with the Queen Mary Ethics of Research Committee, written informed consent will be obtained from participants online.

## Materials

Experimental stimuli and role nouns have been selected based on a corpus collected from online Egyptian recruitment websites [11] and a large scale norming study on occupational stereotypes [35]. These roles were then cross-checked on Sketch Engine to ensure that none of the roles selected are low frequency. For an occupation to qualify as stereotypically female, it has to be typically advertised to women and advertised in feminine grammatical gender (such as *nurse* and *secretary*). Similarly, these roles on Sketch Engine were more likely to appear in feminine G-gender compared to their masculine counterpart, which further validates the stereotypicality of the role. For stereotypically male roles, the same approach was adopted, and occupations were selected if they mostly (at least 70%) targeted men and used masculine grammatical gender (such as *lawyer* and *manager*).

There were two main challenges when selecting the experimental stimuli. Firstly, the gendered stereotypes need to hold cross-culturally for both Egyptian and British participants. Secondly, as the existing corpus and literature has shown, Egyptian online recruitment is heavily gender segregated and polarised. Consequently, finding ‘neutral’ roles in the corpus proved to be difficult and therefore 3 of the neutral stimuli were selected based on other norming studies’ classifications [3, 35].

To mitigate these challenges and ensure that the stereotypes match the attitudes of the target sample(s), additional norming during the piloting stage will be conducted. This will consist of a simple questionnaire to be circulated amongst an Egyptian and British sample (n = 10 for each) asking participants to rate the occupations selected (this includes 4 plus an additional 2 ‘back-up’ role nouns in each stereotype) as stereotypically male, female, or neither on a 7-point scale. Role nouns with stereotypes that do not hold cross-culturally will be excluded from the experiment, with the target of having 4 occupations for each stereotype.

Non-experimental stimuli will include animals (such as *cat*) and will be G-gender balanced with 2 nouns presented in feminine G-gender and 2 presented in masculine G-gender.

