Thus far this research has been relatively limited to ‘Western’ contexts. This study aims to extend this research on grammatical gender and to test whether masculine generics in other language families, specifically Arabic, behave similarly to Indo-European languages. Arabic is one of the most spoken languages around the world, and yet research on the processing of Arabic grammatical gender remains relatively understudied. Additionally, the use of masculine generics in Arabic speaking countries, especially in the context of job recruitment and formal settings, is largely unquestioned and widely accepted as equally representative of all genders. However, a recent study on the language used in Egyptian job recruitment and advertising showed an overuse and inconsistent use of masculine generics, where stereotypically male-dominated industries used masculine generics and stereotypically female-dominated jobs were advertised in feminine grammatical gender regardless of the gender targeted for the role [11]. Additionally, the study showed that jobs were advertised in both singular (majority) and plural masculine generics, and so a key aspect of this investigation is to determine whether masculine generics in singular or plural are interpreted more or less strongly as male-referring. Therefore, the overall aim of this study is to explore how the presence or absence of grammatical gender affects gender representation in perception.

Specifically, the primary objective of this study is to investigate the role that morphological gender marking plays in either entrenching or perhaps mitigating these segregated and polarised recruitment patterns. To do so, we explore the following questions:

1. How does grammatical gender mediate referent expectations in the presence of competing social information?
a. Do singular masculine generics create a male bias in perception, and are these biases different in singular and plural masculine generics?b. Do participants rely more on stereotypical social information or grammatical information to inform their occupational expectations?c. If the social and grammatical cues conflict, do participants exhibit processing costs? Or is there a processing benefit to having congruent social and grammatical cues? And are these benefits or costs consistent across different gender and cue-type combinations?

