## Piloting

This experiment will be piloted in one round if there are no adjustments necessary based on the piloting. However, if changes are required based on the initial pilot, an additional smaller round of piloting will be conducted, and size will be determined based on the magnitude of the change. For example, if the change only affects block 5, other blocks will not be subject to additional piloting. In the first round, blocks 1–3 will be piloted with 3 participants each, block 4 will be piloted with 4 participants, and block 5 will be piloted with 6 participants (3 Egyptian bilinguals and 3 English monolinguals). Based on the initial pilot, the following changes can be made. Firstly, stimuli will be changed (if necessary) based on the stereotype norming exercise. Secondly, the time allocated to participants to produce speech can be increased or decreased from the initial 20 seconds if this is found to be insufficient or too abundant. If no changes are made based on the pilot, the participants’ observations will be included in the analysis.

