## Pre-specified analysis plan

The study uses mixed effects regression, modelled in STATA, to account for within and between variation in the experiment. There are two different outcome categories and therefore multiple models will be used to explore the effect of language on the dependent variables outlined above.

The first set of models related to fluency will utilise linear-mixed-effects models, and models related to gender expectations will use generalised linear mixed effects models for categorical dependent variables. In both cases, the language condition will be defined as the fixed effect. The models will include random slopes for this fixed effect as some occupations may be more affected by the language condition than others. By-participant random slopes and intercepts will be included in the models as random effects. This is because participant variation is expected due to differences in demographic information (age and gender), attitudes towards women (from the exit survey), language dominance measures (exit survey), and participant’s nationality (note that this is likely corelated with attitudes towards women, and highly correlated with language dominance measures). Similarly, by-item random slopes and intercepts will be included as variation due to length of stimuli or familiarity with different occupations should be accounted for.

Interaction effects will be explored between stereotype and language condition, and for a subsample of the data interactions between number and stereotype will also be explored. Interaction effects related to number will help assess the mediating effect of number on gender expectations in masculine grammatical gender.

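### The plan neither balances male and female role nouns on stereotype strength nor uses the noun ratings in the analysis, so a strength difference can enter the question 1c asymmetry

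*Protocol article*

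**What the plan says.** All references are to the protocol article.

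- **Selection (Materials).** For a female noun, "it has to be typically advertised to women and advertised in feminine grammatical gender". For male nouns, described as chosen by the same approach, "occupations were selected if they mostly (at least 70%) targeted men and used masculine grammatical gender".
- **Norming (Materials).** A questionnaire goes to "an Egyptian and British sample (n = 10 for each"), who rate four nouns plus two back-ups per class "as stereotypically male, female, or neither on a 7-point scale".
- **Use of the ratings.** Two uses are stated. In Materials: "Role nouns with stereotypes that do not hold cross-culturally will be excluded from the experiment". In Piloting: "stimuli will be changed (if necessary) based on the stereotype norming exercise".
- **Analysis.** The Design section defines stereotype as three classes of four nouns. The Pre-specified analysis plan says "Interaction effects will be explored between stereotype and language condition". It adds by-item random intercepts and slopes and names no noun-level rating.
- **Question 1c (Introduction).** After asking about costs of conflicting cues, it asks: "are these benefits or costs consistent across different gender and cue-type combinations". The Hypotheses section adds that a generic reading of the masculine should be less costly than a true violation of expectation.

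**The concern.** The cross-cultural filter asks whether a noun's stereotype points the same way in both countries. It does not ask how strong the stereotype is, or whether the four male nouns are on average as strongly stereotyped as the four female nouns.

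Question 1c is a comparison across those two sets. If a stronger stereotype brings a larger cost when the form conflicts with it, a gap in mean strength produces unequal costs by itself. Weaker female nouns would make the masculine look cheap, as a generic masculine would. Stronger female nouns could hide a masculine that really is less costly. Either way, a property of the chosen nouns could be reported as a property of the grammar.

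**Working it through.** **1. Design inputs.** Sample size reproduces: 4 × 30 + 30 + 30 = 180. In Table 2 each noun appears once in each form across blocks 1-3, so at 30 participants per block each noun gets 30 masculine and 30 feminine responses. Noun main effects therefore cancel within a noun.

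**2. The 1c contrast.** Let F be the feminine-minus-masculine cost unrelated to stereotype, b the congruence cost per scale point, and s the mean distance of a noun set from the scale midpoint.

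- Male nouns, feminine − masculine: F + b·s_male
- Female nouns, masculine − feminine: −F + b·s_female
- Difference: 2F + b·(s_male − s_female)

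The last term remains when F = 0. By-item slopes model noun-to-noun deviations with mean zero. They widen the standard error but leave the difference between class means in place.

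**3. Size of the term.** The protocol gives no ratings, so these inputs are assumptions: residual SD 1, b = 0.1 to 0.3 SD per point, SD of strength within a class 0.3 points.

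- Gap 0.5 (1.5 against 2.0): 0.5 × 0.1 to 0.5 × 0.3 = 0.05 to 0.15 SD
- Gap 1.0 (1.5 against 2.5): 0.10 to 0.30 SD

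For scale, residual noise alone gives the contrast a standard error of √(2/30) × √(2/4) = 0.18 SD.

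**4. False positives.** Table 2 was simulated with F = 0 and a two-sided alpha of 0.1 (the protocol gives 0.1 without sidedness), using a by-item test as a stand-in for a model with by-item slopes. Ranges cover two runs.

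| Mean strengths | b = 0.1 | b = 0.2 | b = 0.3 |
|---|---|---|---|
| Equal (2.0, 2.0) | 10% | 10-11% | 10% |
| Gap 0.5 | 11% | 14-15% | 17-18% |
| Gap 1.0 | 14% | 24-25% | 40% |

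**5. With the rating in the model.** For each noun, regress feminine − masculine on its signed, midpoint-centred rating (male positive). The value at rating zero estimates F. Example with F = 0, b = 0.2, strengths 1.5 and 2.0:

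- Class means: +0.30 (male) and −0.40 (female)
- Class-based asymmetry: 0.30 − 0.40 = −0.10
- Slope: 0.70/3.5 = 0.20
- Value at the midpoint: 0.30 − 0.20 × 1.5 = 0

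With ratings averaged over 10 raters (assumed rating SD 1.5), the simulated false-positive rate returns to about 9-11%.

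**6. Precision of the ratings.** For an assumed rating SD of 1 to 2, a noun mean has a standard error of 1/√10 = 0.32 to 2/√10 = 0.63.

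- Within a class (strength SD 0.3), reliability is poor: 0.09/(0.09 + 0.10) = 0.47 down to 0.09/(0.09 + 0.40) = 0.18.
- Across classes at ±2 points it is 4/(4 + 0.10) = 0.98 down to 4/(4 + 0.40) = 0.91.

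The signed-rating slope is identified mainly across classes, so the second pair governs.

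**The case against.** Much of the case on the other side stands.

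- **Unequal selection rules.** A reader might infer that only male nouns met a numerical threshold. Materials introduces the male rule as the same approach and reports a corpus check on the female nouns, so the text does not establish different criteria. The point does not need this: a shared 70% floor would not equalise strength above the floor.
- **The reading of an asymmetry.** A reader might infer that the protocol credits any difference to the masculine. It does not. Hypotheses also expects costs in the feminine because those forms are rarer. The test in Outcomes of interest, whether the masculine on female nouns has a cost at all, cannot be given a false cost by unequal strength if the masculine is truly generic. The exposed part is the comparative reading in 1c and Hypotheses.
- **Equal strength imposed by the model.** It is not. By-item slopes let nouns differ, and the interaction leaves the class effects free. What is missing is a way to separate strength from grammar when those class effects are compared.
- **The rating as primary predictor.** Table 5 and Hypotheses predict that neutral nouns behave like male nouns in the masculine, and Table 5 puts them with female nouns in the feminine. A single linear term cannot represent that step pattern, so the class model should stay primary.
- **Use left to a fuller plan.** A fuller analysis plan could add a use of the ratings. The article does, however, state both the uses and the form of the stereotype factor.

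The Latin square does not answer the point, because it cancels noun main effects only. The stereotype beliefs in Participants' characteristics are measured per person, not per noun.

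**Conclusion.** The concern holds in a limited form. As written, the 1c comparison cannot distinguish a grammatical asymmetry from a difference in mean stereotype strength between the male and female nouns. That follows from the algebra, provided that cost rises with strength.

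The size is not known. Under the assumptions above, false positives at alpha 0.1 are roughly 11-18% for a gap of 0.5 points and 14-40% for a gap of 1 point. At equal strength there is no inflation. Nothing in the protocol shows that a gap exists or which set is stronger, so it would be wrong to conclude that the 1c result will be biased, or in which direction.

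**What to change.** 1. Keep the three-class stereotype × language model as primary.
2. Where more than four nouns per class survive the cross-cultural filter, choose the four so that the male and female sets have similar mean distance from the scale midpoint on the Egyptian ratings.
3. Pre-specify a sensitivity analysis for 1c over the male and female nouns, replacing class with the signed, midpoint-centred Egyptian rating × language. Read the asymmetry as the feminine-masculine difference at the midpoint. In the English block, use each group's own country ratings, since Participants' characteristics expects some stereotypes to be less salient in the UK.
4. Claim a grammatical asymmetry only if it persists in that analysis.

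**Cost.** No new data: the ratings and two back-up nouns per class are already planned, and norming precedes main data collection. The work is one item-level covariate and one extra model.

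**Limits.** Means of 10 raters are imprecise, so balancing on them is approximate and may be impossible if the filter leaves few nouns. The sensitivity model assumes linearity. It reduces the confounding and does not abolish it. It also does not separate grammar from the lower frequency of feminine forms, which sits in F.

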## Piloting

This experiment will be piloted in one round if there are no adjustments necessary based on the piloting. However, if changes are required based on the initial pilot, an additional smaller round of piloting will be conducted, and size will be determined based on the magnitude of the change. For example, if the change only affects block 5, other blocks will not be subject to additional piloting. In the first round, blocks 1–3 will be piloted with 3 participants each, block 4 will be piloted with 4 participants, and block 5 will be piloted with 6 participants (3 Egyptian bilinguals and 3 English monolinguals). Based on the initial pilot, the following changes can be made. Firstly, stimuli will be changed (if necessary) based on the stereotype norming exercise. Secondly, the time allocated to participants to produce speech can be increased or decreased from the initial 20 seconds if this is found to be insufficient or too abundant. If no changes are made based on the pilot, the participants’ observations will be included in the analysis.

## Pre-specified analysis plan

The study uses mixed effects regression, modelled in STATA, to account for within and between variation in the experiment. There are two different outcome categories and therefore multiple models will be used to explore the effect of language on the dependent variables outlined above.

The first set of models related to fluency will utilise linear-mixed-effects models, and models related to gender expectations will use generalised linear mixed effects models for categorical dependent variables. In both cases, the language condition will be defined as the fixed effect. The models will include random slopes for this fixed effect as some occupations may be more affected by the language condition than others. By-participant random slopes and intercepts will be included in the models as random effects. This is because participant variation is expected due to differences in demographic information (age and gender), attitudes towards women (from the exit survey), language dominance measures (exit survey), and participant’s nationality (note that this is likely corelated with attitudes towards women, and highly correlated with language dominance measures). Similarly, by-item random slopes and intercepts will be included as variation due to length of stimuli or familiarity with different occupations should be accounted for.

Interaction effects will be explored between stereotype and language condition, and for a subsample of the data interactions between number and stereotype will also be explored. Interaction effects related to number will help assess the mediating effect of number on gender expectations in masculine grammatical gender.

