### Outcomes of interest

To answer the research questions outlined above, the study focuses on two outcome categories: fluency measures and the participant’s gender interpretation of the prime.

Fluency measures consist of 5 dependent variables: the total number of words produced, hesitation markers, number of false starts, fluency mistakes, and initial response time. These measures are consistent with current literature on speech production [34]. The focus on fluency allows for exploration of processing costs and benefits due to in/congruent or asymmetric stimuli. Additionally, fluency measures help show what is easily accessed or recalled. Processing benefits are expected when participants’ S-gender expectations are not violated (i.e., a *secretary* in feminine morphology and a *manager* in masculine morphology compared to a *secretary* in the masculine). Importantly however, roles associated with women presented in masculine morphology should *not* result in processing costs if masculine G-gender is truly interpreted as generic or unmarked.

To measure the participant’s interpretation of the prime their responses will be coded based on the proportion of gendered morphosyntactic markers in their speech. Importantly, this will be weighted at the tensed phrase (TP) level. This is to avoid inflating scores based on morphosyntactic markers for the sake of agreement across noun phrases or verb phrases. This coding will be used to derive two other categorical variables to be used in the analysis: the participant’s gender expectations and whether the expectations are congruent with the social stereotype associated with the prime.

Example 3 provides a fictitious response to the stimulus “*manager [+masc]*” and how this would be coded. Firstly, we can see that there are three morphosyntactic markers that are masculine, two of which are used only for agreement purposes. Secondly, we can determine that the participant interpreted the stimulus to be a man and that this response is congruent with the prime (i.e., grammatical gender and social gender are not asymmetric).

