Similarly, in condition 4 (neutral English), stereotypical information may inform participants’ gender expectations, such that *doctors* are more likely to be men and *secretaries* are more likely to be women in responses. If this is the case, then the fixed effect for language in conditions 3 and 4 should not be statistically different. Importantly, in this condition participants have the option to respond in the gender neutral ‘they’ instead of assuming the role’s gender. Therefore, some variation between feminine, masculine, and neutral pronouns could be expected. If this condition also elicits highly gendered responses based on social stereotypes, then this presents evidence on the importance of gender-fair and representative language rather than just neutral language. This has implications for jobs advertised in English, which are assumed to be gender-neutral in interpretation but may instead entrench participant’s existing stereotypes.

Additionally, it is expected that fluency measures in congruent conditions will exhibit processing benefits (i.e., fewer fluency mistakes, more speech produced within the time limit, less hesitation, and reduced lag time) compared to their incongruent counterparts. Where grammatical information and stereotype information are incongruent (i.e., *nurse* presented in the masculine or *manager* presented in the feminine), it is predicted that outcomes related to fluency and initial response time will be negatively affected and participants will experience processing costs as a result of a violation of expectations. Importantly, interpreting masculine G-gender as generic should not be as costly or inefficient because it can be used to refer to male or female S-genders.

Further, condition 3 should not show significant differences in fluency or response time due to stereotype or number variation. This is because G-gender and stereotype information can always be congruent in a word-pair. Similarly in condition 4, it is predicted that fluency and response time will not vary across stereotype or number.

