### Data processing & cleaning

In this section we describe how we handle outliers, missing data, and model specification. Firstly, given the presence of by-item and by-participant slopes and intercepts, outliers are less likely to be problematic for the analysis. However, as an additional check, using the *extremes* command on STATA for all numeric outcomes (i.e., fluency measures) we will initially check for cases with extremely high or low values. If any extreme values are identified, they will be investigated further by checking their residuals and leverage. A sensitivity analysis will be conducted to determine whether outlier data will be included or excluded in the analysis. If results are heavily affected by the inclusion of an outlier (and there is no evidence to suggest that differences in results are not random) then this data will be excluded from the analysis.

Secondly, if there is more than 5% of the data missing, this will be further investigated to check if by-item attrition is systematic or randomly distributed. If it is randomly distributed, then these missing observations are automatically removed by STATA in analysis. However, if the missing observations are systematic (e.g., most of the missing data is in response to one particular occupation or stimuli) then this will be investigated further and potentially dropped from the analysis.

Finally, to avoid an overspecification of the models, models that include interactions as predictors will be compared to a simplified model that excludes these interactions using the Bayesian Information Criterion (BIC). The BIC will be used to determine if the unrestricted or restricted model is a better fit for the data.

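### Linear models for per-prompt fluency counts cannot separate more error-prone speech from less speech, and the plan predicts both in the same cells

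*Protocol article*

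**What the plan says.** The Outcomes of interest section lists five fluency variables: "the total number of words produced, hesitation markers, number of false starts, fluency mistakes, and initial response time". False starts are expressly a number, and words produced a total. Hesitation markers and mistakes are named without any denominator. The gender outcome in the same section is normalised: responses are "coded based on the proportion of gendered morphosyntactic markers in their speech", with weighting at the tensed-phrase level.

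The Pre-specified analysis plan then says: "The first set of models related to fluency will utilise linear-mixed-effects models". On predictors it adds: "In both cases, the language condition will be defined as the fixed effect". Stereotype-by-language interactions are to be explored, and random slopes and intercepts are planned by participant and by item. No offset, per-word rate or word-count covariate is mentioned. The Data processing & cleaning section treats the fluency measures as plain numeric variables: "for all numeric outcomes (i.e., fluency measures) we will initially check for cases with extremely high or low values".

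The Hypotheses section expects congruent prompts to bring "fewer fluency mistakes, more speech produced within the time limit, less hesitation, and reduced lag time". For incongruent prompts, "it is predicted that outcomes related to fluency and initial response time will be negatively affected". Table 5 sets this out cell by cell. In the two incongruent cells (female-stereotyped roles in the masculine, male-stereotyped roles in the feminine), words are low, while mistakes, false starts, hesitations and response time are high.

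On missing data, the plan looks into the pattern when more than 5% is missing. If the pattern is random, "these missing observations are automatically removed by STATA in analysis". If it is systematic, the data are examined further and may be dropped.

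**The concern.** Research question 1c asks whether conflict between grammatical and social cues carries a processing cost. Three of the five fluency outcomes (hesitations, false starts, mistakes) are measures of disfluency, and the opportunity for at least some of these events depends on how much is said. The plan predicts that the amount said will fall in just the cells where disfluency should rise. If errors accumulate with words, the two predicted effects pull the per-prompt count in opposite directions. A flat or falling count would then be read as no cost, even though the speech that was produced had become more error-prone.

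Two related points follow from the same modelling choice. Counts per short prompt may be small and skewed with many zeros, which a linear model describes poorly. And a prompt that elicits no speech, arguably the largest processing cost, has no response time. The plan does not say how such a prompt is scored.

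**Working it through.** **Inputs.** From the article: an initial window of 20 seconds for every prompt, linear mixed models for all fluency outcomes, and the predicted directions in Table 5. Word counts, error rates and their variances are not given, so every value below is an assumption. The article has no figure of its own on this point to reproduce.

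**Identity.** Expected errors per prompt = words × errors per word. Hence

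count ratio = word ratio × per-word rate ratio.

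If the per-word rate does not depend on the number of words, the count rises only when the rate ratio exceeds 1 / (word ratio). The break-even rise in the rate is therefore 1 / (1 − drop) − 1:

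| Fall in words | Break-even rise in per-word rate |
|---|---|
| 10% | 1/0.9 − 1 = 11% |
| 20% | 1/0.8 − 1 = 25% |
| 30% | 1/0.7 − 1 = 43% |
| 40% | 1/0.6 − 1 = 67% |

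**Example of reversal.** Congruent: 30 words × 0.05 = 1.50 mistakes. Incongruent: 24 words (−20%) × 0.06 (+20%) = 1.44. The count falls by 4% while the rate rises by 20%.

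**Examples without reversal.** Words −20%, rate +50%: 0.8 × 1.5 = 1.20. Words −10%, rate +20%: 0.9 × 1.2 = 1.08. The sign is right, but the rise in the per-word rate is understated.

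**Illustrative simulation.** Assumptions: 90 participants, 4 congruent and 4 incongruent prompts each, 30 words per congruent prompt, 0.10 errors per word, Poisson counts with variation between participants, two-sided alpha 0.1, 200 runs per scenario. The raw-count analysis is the mean within-participant difference, which in this balanced layout equals the linear mixed-model fixed effect. The comparison is a Poisson model (fitted by generalised estimating equations) with log(words) as offset.

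| Words | True rate | Mean count difference | Significant rise | Significant fall | Rate ratio with offset |
|---|---|---|---|---|---|
| −10% | +20% | +0.24 | 52.5% | 1% | 1.20 |
| −20% | +20% | −0.10 | 0.5% | 21% | 1.21 |
| −30% | +20% | −0.49 | 0% | 100% | 1.20 |
| −30% | +30% | −0.29 | 0% | 72.5% | 1.29 |
| −20% | +50% | +0.60 | 100% | 0% | 1.50 |

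The simulation builds in proportionality between errors and words. It shows the consequence of that assumption and does not test it.

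**Zeros.** At an assumed mean of 0.3 false starts per prompt, a Poisson count is zero with probability exp(−0.3) = 0.74.

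**Standard errors.** In a separate check with gamma-Poisson counts, 90 participants, 4 + 4 prompts, no item effects and 5,000 runs, nominal 90% intervals for the linear mean difference covered about 90% at means of 0.3 against 0.3 and 0.3 against 0.36. At 0.3 against 0.6, coverage was about 87% with one constant residual variance, but about 90% from participant-level differences, which correspond to the by-participant random slopes that the plan includes.

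**The case against.** The strongest reply is that Table 5 makes no per-word prediction. It predicts numbers of false starts, hesitations and mistakes, and every prompt has the same window, so a per-prompt count is a legitimate rate per unit of time and estimates what the table states. This stands. A reader might infer that three of the five fluency tests are biased against their hypotheses. The documents do not support that: the distortion concerns the per-word rate, which is a different quantity.

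Proportionality is also doubtful for hesitations. They use up time and may precede the first word; the Hypotheses section itself expects initial hesitation over agreement in the word-pair condition. More hesitation may be the cause of fewer words. This stands too, and it is why a per-word rate should not replace the count. It does not remove the ambiguity of the count when words are predicted to change.

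A reader might further infer that the linear model's standard errors are wrong. This is not shown; with the planned by-participant slopes, the check above found coverage near nominal. The case for count models rests on fit to sparse, skewed data.

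Nor does the plan say that silent prompts are discarded. Automatic removal is tied to random missingness, and zero words is an observed value. Only response time is undefined, and its handling is left open. Finally, scoring of hesitations and mistakes as counts is inferred from the article's silence. A fuller protocol could define them otherwise, but the model class itself is fixed here.

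**Conclusion.** The point holds in a limited form. The plan fixes a linear model for outcomes that are counts, or very probably counts. It offers no means of separating error-prone speech from reduced speech, although its own hypotheses predict both in the incongruent cells. If errors scale with words, a fall in words of 10% to 30% hides any rise in the per-word rate of up to 11% to 43%. Larger rises appear with the right sign but attenuated. Reversal is possible and not inevitable, and the sizes are illustrative for want of word counts and error rates in the article. The denominator argument does not touch words produced or response time. The change is worth making because it affects how three of the five fluency outcomes bear on question 1c and costs little.

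**What to change.** 1. Analyse words produced, hesitations, false starts and mistakes with Poisson or negative binomial mixed models in place of linear ones, and state how hesitations and mistakes are scored.
2. For hesitations, false starts and mistakes, report two summaries: the count per prompt, and the rate per word from a model with log(words) as offset. Restrict the second to prompts with at least one word, because log(0) is undefined.
3. Interpret question 1c from both summaries together with words produced.
4. Score silent prompts as zero words, and treat their response time as censored at the time limit in a log-scale or survival-type model, so that they do not drop out as missing.

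The cost is analysis-plan wording; no new data or participants are needed. Fits will be slower, and there are two error summaries where there was one. The per-word rate conditions on words, which are themselves an outcome of the prompt, so it complements the per-prompt count and cannot stand in for it.
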